# From cars to bikes – the feasibility and effect of using e-bikes, longtail bikes and traditional bikes for transportation among parents of children attending kindergarten: design of a randomized cross-over trial

**DOI:** 10.1186/s12889-017-4995-z

**Published:** 2017-12-28

**Keywords:** Active transportation, E-bike, Cargo bike, Bicycling time, Bicycling distance, Physical activity, Fitness, Body composition

## Abstract

**Background:**

The present study aims to increase bicycling and level of physical activity (PA), and thereby promote health in parents of toddlers, by giving access to different bicycle types. There is a need for greater understanding of e-bikes and their role in the transportation network, and further effects on PA levels and health. Moreover, longtail bikes could meet certain practical needs not fulfilled by e-bikes or traditional bikes, hence increased knowledge regarding their feasibility should be obtained. No previous studies have investigated whether providing an e-bike or a longtail bike over an extended period in a sample of parents of toddlers influence objectively assessed amount of bicycling and total PA level, transportation habits, cardiorespiratory fitness, body composition and blood pressure.

**Methods:**

A randomized cross-over trial will be performed, entailing that participants in the intervention group (*n* = 18) complete the following intervention arms in random order: (i) three months access to an e-bicycle with trailer for child transportation (*n* = 6), (ii) three months access to a longtail bicycle (*n* = 6), and (iii) three months access to a regular bicycle with trailer (*n* = 6), in total nine months. Also, a control group (*n* = 18) maintaining usual transportation and PA habits will be included. A convenience sample consisting of 36 parents of toddlers residing in Kristiansand municipality, Southern Norway, will be recruited. Total amount of bicycling (distance and time), total level of PA, and transportation habits will be measured at baseline and in connection to each intervention arm. Cardiorespiratory fitness, body composition and blood pressure will be measured at baseline and post-intervention. Main outcome will be bicycling distance and time spent cycling.

**Discussion:**

New knowledge relevant for the timely issues of public health and environmental sustainability will be provided among parents of toddlers, representing a target group of greatest importance. There is a call for research on the influence of e-bikes and longtail bikes on travel behavior and PA levels, and whether voluntary cycling could improve health. If the present study reveals promising results, it should be replicated in larger and more representative samples. Eventually, inclusion in national public health policies should be considered.

**Trial registration:**

ID NCT03131518, made public 26.04.2017.

## Background

### Physical activity levels and active transportation

It is well documented that regular physical activity (PA) implies reduced risk for overweight and chronic diseases [1]. Still, one third of adults and four fifths of adolescents globally do not reach PA guidelines [2], and recent European data showed that only 28% of the adult population comply with the PA recommendations [3]. Nonetheless, only ten additional minutes of PA daily would make two thirds of inactive persons adhere to current PA guidelines [4].

For our ancestors, food procurement was inextricably linked to PA and energy expenditure [5], as they needed to hunt and forage in order to get food. Today, this link is broken- we can drive our car to the grocery shop and buy the foods we need with minor energy expenditure. In turn, these changes imply that being physically active requires conscious choices to a larger degree. Physical inactivity is estimated to cause approximately 6–10% of the non-communicable diseases of coronary heart disease, type II diabetes, breast- and colon cancer, and 9% of premature deaths worldwide, i.e. similar health effects as the established risk factors of obesity and smoking [6]. Car use and other forms of motorized transportation favour neither health nor environmental sustainability, as it entails sedentariness and emissions of greenhouse gases (GHGs).

Active transportation, like walking or cycling for transportation purposes, may be a feasible and time efficient way to incorporate PA into daily routines, potentially increasing PA levels [7, 8]. Thus, active transportation could promote health [7, 9–15], prevent obesity [16, 17], and decrease future healthcare costs [18]. It has been calculated that increased PA would translate into significant health gains, entailing major socioeconomic gains for the society [19]. For bicycling specifically, a tripling in cycling in five urban areas in Norway between 2006 and 2009 has been estimated to imply health benefits of 250 million NOK annually [20].

Next to direct effects on fitness and health, an additional advantage of active transportation is the potential to decrease GHG emissions [21, 22], as well as noise and pollution [7]. Currently, motorized transportation is responsible for about 23% of global climate gas discharges [7]. The ambitious goal of the Paris Agreement, entailing carbon neutrality before the end of the century [23], demands initiatives to be generated within all areas of society, not the least within the transportation sector. It is likely that an increased share of travels in Norway could be conducted as active transportation, considering that 25% of daily travels done by car are shorter than 2.5 km [20], and average distance of bicycle trips is 5.1 km [24]. Accordingly, 20% of all travels in the UK are shorter than one mile [25].

### Parents as facilitators of physical activity

Lifestyle behaviors in childhood constitute the foundation for health throughout the lifespan, and research suggests that lifestyle habits, such as PA, track from childhood into adulthood [26, 27]. Likewise, overweight and obese children are more likely to become overweight and obese adults, than normal weight children [28, 29]. Parents are important facilitators and role models of PA for their kids, and among the significant correlates are parental PA, as well as parent participation in child PA [30]. Being transported to kindergarten by bicycle instead of by car could teach children that alternative modes of transport exist, hence representing early adaptation to healthy and sustainable transportation and PA habits. Since parental PA behaviors are crucial for their own and their children’s current and future health, parents of toddlers is a target group of utmost importance. In terms of parental own PA habits, lack of time [31] and stress [32] are repeatedly documented to be negatively associated with PA in adults. In this regard, active transportation could potentially decrease the impact of time scarcity as a barrier, and may also reduce overall perceived stress through incorporating PA into daily transportation, implying less need for additional time-consuming exercise.

### E-bikes and longtails

Electric assisted bicycles (e-bikes) represent an unexploited potential in terms of increased bicycle use. If replacing other motorized modes, and not replacing other PAs, e-bikes could favor both public health and the environment through increased levels of PA and decreased emissions of climate gases [22, 33]. Empirical evidence indicates that mode substitution depends on local context, culture and available transport alternatives, entailing that a larger proportion of car trips is replaced in cardominated countries such as Australia, US and Canada, than in countries with a bicycle culture, such as Denmark and the Netherlands [34]. For illustration, recent Dutch data showed that e-bike ownership reduced car and public transport use, although usage of the traditional bike decreased even more [35]. Nonetheless, e-bike owners reduced their car and public transport use more than traditional bicycle owners [35]. Moreover, in a convenience sample of Norwegian car owners, it was found that those who cycled the least were most interested in buying an e-bike, which in turn could result in mode shifts from cars to bikes [36].

In e-bikes categorized as pedelecs, propulsion is caused partly from the pedal- power of the rider, and partly from an electric engine supplementing power up to 25 km/h, or a maximum power output of 250 watt [34]. It has been claimed that energy efficiency of an e-bike is greater than that of any other mode of transport, except from traditional bicycles [37]. Compared with regular bicycles, e-bikes enable maintenance of speed with less effort, which in turn helps overcoming some of the most common barriers to traditional pedal cycling, such as lack of fitness needed to cycle, hilly terrain, longer distances, lack of time, and lack of end of trip facilities (e.g. change rooms and shower) [34]. Current knowledge suggests that e-bike users cycle more often, and to more distant locations than those using regular bicycles [34, 37, 38], hence possessing greater capacity for exchanging car use than regular bicycles.

A major limitation with traditional bicycles, and also standard e-bikes, is the carrying capacity [39]. At present, there are several different cargo bikes on the market, both human powered and with electric assistance, as well as various bike trailers for carrying goods and/or children. However, carrying stuff on a trailer may be less convenient than directly on a bike. In this regard, so-called longtail bikes possess a great potential, being constructed for carrying an adult, two children and additional goods. Such longtails could possibly promote health through increased cycling, and reduce anthropogenic CO_2_ emissions related to motorized transportation, while simultaneously meeting a practical need not sufficiently accomplished by a traditional bike or e-bike. Considering that a great share of car travels are done within a limited range [20, 25], longtail bikes might represent a feasible mode of transportation, yet current scientific evidence is scarce. Still yet, our research group has tested human powered longtail bikes in different families for periods lasting up to five years, elucidating the potential of longtails for various trip purposes, and for all seasons and weather conditions. In line with this, American data support possible mode substitution and a decline in car travel among cargo bike owners [40]. Giving specific attention to females with children, representing a minority group in the bicycling community, Schwartz and Riggs [41] newly suggested that under certain circumstances and subject to a certain culture, the cargo bike has emerged as an option for women to choose.

### Health effects of e-bicycling and use of longtails/transport bikes

It is repeatedly found that both active [42] and inactive [43, 44] subjects reach PA levels sufficiently high to meet the moderate-to-vigorous-intensity standard (3–9 metabolic equivalents (METs)) of the physical activity guidelines [1, 45], when e-biking. Although e-bikes seem to entail lower intensity than traditional bikes [46], e-bikes could still boost overall levels of PA [34] and thereby promote health, if combined with more frequent and longer trips as proposed [37, 38]. Current evidence regarding health effects of commuting with an e-bike is scarce. De Geus and colleagues [47] conducted a quasi-experimental study in twenty untrained men and women, who were provided with an e-bike for six weeks. No change in maximum oxygen uptake (VO_2_ max) was found, yet a significant gain in maximal power output was achieved after six weeks of e-biking [47]. A recent Norwegian pilot study equipped 25 inactive adults with an e-bike for eight months, measuring participants′ VO_2_ max at baseline and at intervention determination [48]. Results showed an average 8% improvement in VO_2_ max, and cycling distance was positively associated with the increase, yet no control group was included. Focus group interviews were conducted and analyzed as well, revealing that e-biking contributed to highly positive experiences regarding active commuting (unpublished results). Moreover, a recent American study in twenty sedentary commuters reported four weeks of pedelec commuting to result in significant improvements in 2-h post-plasma glucose levels, VO_2_ max and maximal power output [49]. In addition, no compensatory changes in overall PA levels were observed, hence pedelec commuting helped the participants to meet PA recommendations [49]. In terms of potential health effects of using human powered longtail bikes or other cargo bikes, no previous studies have addressed these associations. It seems reasonable to assume though [46], that the intensity will be higher than for traditional bikes due to the weight of the cargo, entailing additional health effects if used as frequently as traditional bikes.

### Accessibility, social support and intrinsic motivation

When developing programs aiming to promote certain behaviors, such as bicycling with e-bikes and longtail bikes, relevant determinants for the behaviors of interest should be known. Existing literature and behavioral theories provide relevant determinants at several levels, that is, the personal (e.g. motivation, intention, knowledge, attitude), interpersonal (social support, modelling) and/or environmental (availability, accessibility, policy) level. The socio-ecological framework suggested by Sallis et al. [50] describes most of these determinants, especially the environmental determinants, while theories such as the Social cognitive theory [51] and the Self-determination theory [52] describe the more interpersonal and cognitive processes to increase goals and motivation for various behaviors, like PA. The Self-determination theory focuses on diverse types of motivation, and argues that intrinsic motivation should be strived for, in order to result in sustained behavior [52]. According to the socio-ecological framework [50], accessibility is one important environmental determinant for PA, including active transportation. Supporting this, a recent British study indicated that when made accessible, e-bikes could facilitate active travel and have substantial effects on travel behavior, also in subjects traditionally undertaking less PA or feeling unable to use a conventional bike [53]. In total 80 employees were loaned an e-bike from two major employers in Brighton, during a six- to eight-week trial period. Across all participants 75% chose to use the e-bike at least once a week, car mileage was reduced by 20%, and 59% of the employees reported that their overall PA increased. At the end of the trial, 73% of the employees said they would cycle to work at least once a week if they had an e-bike available [53]. Bike share programs may be considered another aspect of accessibility, and a number of cities have now introduced e-bike shares, potentially encouraging new users to bike share [54]. Underpinning this, a pilot study trialing a university based e-bike share in North-America reported that new users were attracted to cycling [55]. Multi-city analyses of regular bike shares’ impact on car use and PA suggest that car use decreases, yet of limited magnitude [56]. Nonetheless, PA levels could increase [57] due to mode shifts, likely resulting in overall positive health effects [58]. Another important behavioral interpersonal determinant described in the socio-ecological framework is social support, and the workplace environment, entailing both the social and the physical environment, could facilitate active transportation [50]. A previous study by Wen and colleagues [59] assessing the role of workplaces in promoting active commuting, reported a significant inverse association between employees’ perception of workplace encouragement for active travel and driving to work. Also, physical support at work, such as available bike parking and presence of showers, as well as cultural and social support for active transportation, has shown to be relevant for female employees’ transport choices [60]. Accordingly, Yang et al. [61] found that worksite support and policies tended to associate with active commuting and the use of public transit. Grounded in this, together with previously reported higher income and education among e-bike owners [62], it is reasonable to assume that initiatives providing bike accessibility could increase cycling. In line with Self-determination theory, we hypothesize that increased accessibility and social support could facilitate intrinsic motivation for biking [52] through meeting the basic psychological needs, i.e. feelings of autonomy, competence and relatedness [63], which in turn could result in higher levels of bicycling.

### Objectives

We aim to assess the effect of an intervention where participants will be provided access to an e-bike (including a trailer), a longtail bike and a traditional bike (including a trailer), each bike for three months, on the following aspects:

#### Primary objectives

Objectively assessed amount of bicycling (distance and time) and total time of moderate-to-vigorous intensity PA (MVPA), assessed at baseline, after three months, six months and nine months (post-intervention).Mode shifts from car to bike, assessed at baseline, after three months, six months and nine months (post-intervention).

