### Study sample

A convenience sample consisting of 36 parents of toddlers residing in Kristiansand municipality, Southern Norway, will be recruited. Main outcome will be total amount of bicycling (distance and time). Due to few previous studies in e-bikes and none in longtail bikes targeting total amount of bicycling, power calculations are challenging to perform. However, based on a standard deviation (SD) of 60 min/week [48], a power of 0.80 and a significance level of 5%, we will be able to detect an increase in cycling time from 15 min (based on inclusion criteria) to 75 min a week (i.e. half of weekly PA recommendations) with 16 subjects in the intervention group and 16 subjects in the control group. Yet, to account for 10% drop-out, and to utilize the bikes optimally according to the study design (see Table 1), we will include 18 subjects in both groups (intervention and control). Inclusion criteria are: (i) being able to understand and read Norwegian, (ii) having one child born in year 2013, 2014 or 2015, attending kindergarten, (iii) being responsible for bringing/picking up the child in the kindergarten ≥5 times per week/at least half of the times, (iv) residing 2–10 km from the workplace, (v) residing <3 km from the kindergarten and the grocery shop, (vi) having car-access (vii) possessing a smartphone requiring personal pin code or comparable safety solution for usage, (viii) being between 167 and 190 cm tall (due to the size of accessible bikes), and (ix) have the opportunity to store the bikes indoors. Exclusion criteria are: (i) being physically active, i.e. meeting the PA recommendations [1, 45], (ii) having bicycled more than once weekly during the last twelve months to the workplace, kindergarten or the grocery shop, and (iii) suffering from severe cardiovascular diseases or upper respiratory tract diseases.

**Table 1 Tab1:** Possible combination of intervention arms

Month 1–3	Month 4–6	Month 7–9	
E-bike	Longtail	Traditional	*n* = 3
E-bike	Traditional	Longtail	*n* = 3
Longtail	E-bike	Traditional	*n* = 3
Longtail	Traditional	E-bike	*n* = 3
Traditional bike	E-bike	Longtail	*n* = 3
Traditional bike	Longtail	E-bike	*n* = 3

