### Quantitative and qualitative data analyses

The statistical analyses for the quantitative data will be performed using the statistical software package IBM SPSS Statistics version 24.0 (IBM Corp., Somers, New York, USA). A two-sided *p*-value of <0.05 will be considered statistically significant. Descriptive analyses will be conducted and continuous variables will be presented as means and standard deviations (SD), categorical variables as proportions. Moreover, regression analyses will be performed according to Twisk and Proper [73], using data from the post-measures adjusting for baseline measures, to assess differences between (1) the control group and the intervention group (between design) for all outcome variables, and (2) within the intervention group when comparing the three different arms regarding total amount of bicycling and PA, transportation habits, and self-reported health and HRQoL.

A qualitative content analysis will be conducted from a phenomenologic-hermeneutic perspective [74]. Recordings of the qualitative interviews will be transcribed verbatim and read repeatedly to grasp the meaning of the data as a whole. Data will then be imported into the software analysis program NVivo 11 for further analysis. The next step will be to separate the text into meaning units; i.e. the words, sentences or paragraphs containing aspects related to each other through their content and context. Following this, the meaning units will be classified into subcategories, by pooling data with similar characteristics together in a category defined by its content. Finally, the subcategories will be combined and categorized into main categories.

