Nonetheless, there are some study limitations. The intervention is quite straightforward, addressing accessibility as one main behavioral determinant, yet reality is more complex. If other determinants are equally or even more important than accessibility, we may not achieve behavior change due to exclusion of these other determinants. Moreover, if effectiveness comes out low, i.e. parents are not bicycling, we will not obtain enough data to draw any conclusions regarding potential health effects from bicycling for transportation. Also, sample size and study power are shortcomings; we expect to detect significant differences in the physiological parameters between the control and intervention group, yet not between the three intervention arms. Still, relevant knowledge regarding total amount of bicycling (main outcome) and PA, as well as travel habits and motivation, is likely to be acquired across the bicycle types. It should be mentioned though, that period effects and carry-over effects could influence these latter aspects, due to the lack of wash-out periods between the intervention arms. Besides, the cross-over design requires a longer study period than a parallel group design, which may increase the drop-out risk. And, because we are recruiting a convenience sample, self-selection and homogeneity is likely to impair generalizability.

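### Four outcomes have primary status in one place and two elsewhere, no measure leads, and only cycling time was sized

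*Protocol article*

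**What the plan says.** The protocol article ranks its outcomes in four places.

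- **Objectives, Primary objectives.** The first item is "Objectively assessed amount of bicycling (distance and time) and total time of moderate-to-vigorous intensity PA (MVPA"). The second is "Mode shifts from car to bike, assessed at baseline, after three months, six months and nine months (post-intervention"). That makes four measures: distance, time, MVPA and mode shift.
- **Abstract, Methods.** "Main outcome will be bicycling distance and time spent cycling". Two measures.
- **Methods, Study sample.** "Main outcome will be total amount of bicycling (distance and time"). Two measures.
- **Discussion, limitations.** The study expects "relevant knowledge regarding total amount of bicycling (main outcome) and PA, as well as travel habits and motivation". The main-outcome label covers bicycling only; physical activity and travel habits stand outside it.

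The sample-size paragraph in Study sample concerns one measure: "we will be able to detect an increase in cycling time from 15 min" to 75 min a week, with an SD of 60 min/week, 80% power and a 5% level. The section on quantitative and qualitative data analyses applies a single threshold, a two-sided p-value "of <0.05 will be considered statistically significant", and runs the intervention-control regression on every outcome variable. It names no lead outcome, testing order or split of the significance level.

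**The concern.** A reader cannot tell from the article whether MVPA and mode shift are primary. Even on the narrower main-outcome wording, the label covers two measures and neither is placed first. Distance, MVPA and mode shift have no stated effect size, SD or power.

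This matters if the measures disagree. Cycling time might miss significance while distance, MVPA or mode shift reaches it. Nothing in the article then says which result carries the main conclusion. The Background notes that e-bikes hold speed with less effort and are ridden to more distant places, so distance and time could well part company. With 36 participants, the choice of deciding measure should not be left until the data are in.

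**Working it through.** **1. The plan's own figure.** Inputs from Study sample: difference 75 − 15 = 60 min/week, SD 60 min/week, power 0.80, two-sided 5%, equal groups.

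n per group = 2 × (1.960 + 0.842)² × (60/60)² = 15.7, so 16. Allowing 10% drop-out: 16 / 0.90 = 17.8, so 18.

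This reproduces the stated 16 and 18. (A t-based version gives 16.7, so 17, which is close enough.) The figure holds for cycling time alone, tested at the full 5%.

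**2. False-positive chance with several primary outcomes.** Take one intervention-control test per outcome, each at two-sided 0.05, with no true effect on any of them. Under independence the chance of at least one significant result is 1 − 0.95^k:

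- k = 2: 1 − 0.9025 = 9.75%
- k = 4: 1 − 0.8145 = 18.5%

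The outcomes are correlated, and the article gives no correlations, so they must be assumed. The table comes from 1,000,000 simulated sets of normal test statistics with equal correlation r, counting sets in which any |z| exceeds 1.96.

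| r (assumed) | two outcomes | four outcomes |
|---|---|---|
| 0.3 | 9.5% | 17.4% |
| 0.5 | 9.1% | 15.6% |
| 0.7 | 8.4% | 13.1% |
| 0.9 | 7.0% | 9.4% |

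For distance and time, r = 0.9 is a sensible working value because both come from the same rides and devices. For all four, a uniform 0.9 is generous: MVPA comes from an armband and transport habits from a questionnaire. A mixed pattern (0.9 for time with distance, 0.4 to 0.5 for either with MVPA or mode shift, 0.3 between those two) gives about 14.6%.

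**3. Cycling time null, another outcome falsely significant.** Cycling time alone accounts for 5 points of each total, so the rest is the chance that it is not significant while another outcome is:

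- two outcomes, r = 0.9: 7.0 − 5 = 2.0%
- four outcomes, r = 0.9: 9.4 − 5 = 4.4%
- four outcomes, r = 0.5: 15.6 − 5 = 10.6%

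**4. Cost of keeping several co-equal outcomes.** Split the 5% equally (Bonferroni) and apply the same standardised effect of 1.0:

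- Two at 0.025: 2 × (2.241 + 0.842)² = 19.0, so 20 per group; 20 / 0.90 = 22.2, so 23 after drop-out. Power with 18 per group is 0.78, and with 16 it is 0.72.
- Four at 0.0125: 2 × (2.498 + 0.842)² = 22.3, so 23 per group; 23 / 0.90 = 25.6, so 26 after drop-out. Power with 18 per group is 0.69, and with 16 it is 0.63.
- One at 0.05: 16 per group, 18 after drop-out, as planned.

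These figures count one test per outcome. The assessments at three, six and nine months and the comparisons among the three bikes are left out.

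**The case against.** The strongest reply is that objectives and outcomes are different things. All three uses of the main-outcome label agree on amount of bicycling, so the text can be read as one lead construct inside a wider set of primary objectives. That is fair, and it rules out saying that the article has no lead outcome at all. It does not settle which of the two measures leads, or whether MVPA and mode shift share primary standing.

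A reader might also infer that the trial may claim success on whichever outcome is significant, or that the plan breaks a promised overall 5% error rate. The article supports neither. It writes no success rule, and its 0.05 is a general per-test threshold, not a family-wise promise. A testing order may also sit in an analysis plan that is not shown. Its absence here is therefore not the complaint; the mismatch in status between sections of the same article is.

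The 18.5% should not be taken as the expected error. It needs independence, which distance and time from the same rides cannot have.

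Finally, this is a small convenience-sample study with feasibility in its title. It admits limited power and asks for replication, so the harm is less than in a confirmatory trial. That lowers the stakes but does not remove the ambiguity.

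**Conclusion.** The point holds in a limited form. The article gives primary standing to four measures under Primary objectives and main-outcome standing to two elsewhere. It names no lead measure and sizes only cycling time.

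Taken as written, the chance of at least one false-positive primary result in the intervention-control comparison is about 7% for distance and time at r = 0.9, and about 9% to 16% for all four at r = 0.9 to 0.5. The upper bound is 18.5%. All of these exceed 5%, but the correlations are assumptions, and the calculation treats each test statistic as normal with no true effect on any outcome.

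The sample-size figure itself is sound.

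**What to change.** - Bring Primary objectives into line with the Abstract, Study sample and Discussion.
- Name weekly cycling time, intervention versus control, as the single primary outcome. It is the only measure with a sample-size basis.
- State one time point for it, or one summary over the nine months. The objectives list three follow-up assessments, so without this there is still more than one candidate primary test.
- Make distance the first secondary outcome, or test it second in a fixed order after time. This keeps its separate information without adding to the error rate of the main claim.
- List MVPA and mode shift as secondary.
- Say that the main conclusion rests on cycling time and that the other outcomes support it.

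The cost is wording in those sections and in the analysis plan; the sample size stays at 18 per group. There are two downsides. Distance, MVPA and mode shift can no longer carry the main conclusion alone. The registry entry, which is not among the documents at hand, must be checked so that the outcome ranking agrees with it.
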